**1. Protocol Summary**

Nearly 40% of epilepsy patients with an unknown etiology and lack effective targeted therapeutic drugs. PFO is known to induce hypoxia and micro-embolism, leading to cerebral neurological dysfunction and increased risk of epilepsy. PFO closure surgery has been introduced into the corresponding clinical guidelines, because of its significant effect in patients with cryptogenic stroke and migraine. The PFOC-RE trail aims to evaluate the efficacy of PFO closure surgery for refractory epilepsy patients, and assesses its potential clinical value of improving epileptic seizures in patients with PFO and epilepsy. Recruitment takes place at the West China Hospital of Sichuan University, China, with started in December 2022 until November 2026, for an open-label, randomized controlled clinical trial. This trial will includes 110 patients diagnosed with refractory epilepsy and PFO, which based on ILAE's diagnostic criteria for epilepsy and ASE's diagnostic criteria for PFO using echocardiography. Eligible patients with epilepsy require a middle (over than 10 microbubbles) or higher volume of right-to-left shunt. Patients will randomly assigned to either surgical intervention group or control group. Patients in intervention group will undergo PFO closure surgery and receive six months of antiplatelet therapy, and will only receive six months of antiplatelet therapy in control group. The primary outcome is the percentage of decline in the frequency of epileptic seizures during the first year after surgery compared to before surgery. Secondary efficacy outcomes include the percentage of decline in the average duration of seizures after surgery, alleviation in the severity of epilepsy, frequency of epileptiform discharge by video EEG, and postoperative quality of life. PFOC-RE is an innovative and clinically significant trail, which aims to identify whether PFO closure surgery can benefit patients with refractory epilepsy and PFO by relieving symptoms and improving quality of life while maintaining a high safety profile.

**2. Background**

Patent foramen ovale (PFO) is the most common congenital heart abnormality of fetal origin, and presents in approximately 25% of adults worldwide[1]. Although PFO has no obvious clinical symptoms, clinical evidences suggest that it is closely associated with migraine, stroke, obstructive sleep apnea and other neurological diseases[2]. In discussing the mechanisms of neurological diseases in patients with PFO, an important viewpoint is that the presence of paradoxical embolization increases the risk of stroke and migraine, and the right-to-left shunt (RLS) mediated by PFO is an important cause of paradoxical embolization[3]. Due to the existence of RLS in the heart, some studies suggest that PFO may play a role in the process of microembolus-triggered cortical spreading depression[4], which is the main theory explaining the aura of migraine[5]. Additionally, other research proposes alternative mechanisms, such as the vasoactive substance hypothesis[6], increased oxygen desaturation index / apne-hypopnea index[7], as well as the discovery of biomarkers, such as serum albumin-bound proteins, to assess the effects of PFO endovascular closure[8]. A blood circulation diagram for PFO patients is shown in Figure 1[2].

[figure not shown]

**Fig.1 Schematic diagram of blood circulation in patients with patent foramen ovale before and after birth.**

Note: PVR, pulmonary vascular resistance; RA, right atrium; LA, left atrium; RV, right ventricle; LV, left ventricle.

Surgical treatment has been the primary method of PFO closure all the time before the development of percutaneous trans-catheter closure, which was associated with poor sealing efficacy and various complications. The first case series reporting successful percutaneous trans-catheter closure of PFO in 36 patients was published in 1992[9], soon after, Schrader reported one of the largest series of PFO trans-catheter closures involving 457 patients, including 169 with atrial septal aneurysm (ASA), from 1994 to 2003[10]. The study demonstrated the great safety and sealing efficacy of this operation. Therefore, the PFO closure though the catheter-based procedures, instead of surgical closure, has become widely accepted among patients and their doctors[11].

The efficacy and safety of PFO closure in patients with stroke, migraine, and other nervous system diseases have been successively confirmed in recent years. Long-term follow-up studies have also shown that most patients who underwent PFO closure through catheter-based procedures not only without serious safety events, but also indeed associated with a lower rate of recurrent ischemic strokes[12], a significant reduction in the mean number of monthly migraine attacks[13], as well as an obvious improvement of dyspnea and hypoxemia[14]. In 2022, evidence-based guidelines from the Society for Cardiovascular Angiography and Interventions provided appropriate patient selection and treatment recommendations for PFO closure in stroke and migraine[15]. A Schematic diagram of foramen ovale closure shown in Figure 2[16].

[figure not shown]

**Fig.2 Schematic diagram of foramen ovale closure.**

Note: Local anaesthesia is first administered at the groin. The femoral vein is then punctured to facilitate venous access, followed by standard guide wire and catheter techniques to access the right side of the heart. Typically, closure of the patent foramen ovale (PFO) is accomplished by implantation of a self-expandable occluder under fluoroscopic as well as intracardiac echocardiography or transoesophageal echocardiography guidance. Peri-procedural imaging of the PFO is not standard. The most widely used device to close the PFO is the double-disc-type occluder. The device catheter first crosses the PFO tunnel. The left-sided disk of the occluder is then completely unfolded and positioned at the left side of the interatrial septum. In a second step, the right-sided disk is unfolded and adopted to the right side of the septum. After verification of a secure and correct placement, the occluder is detached from the catheter and the remaining catheter material is retrieved. LA, left atrium; RA, right atrium

Epilepsy is one of the most prevalent neurological diseases, affecting approximately 69 million people worldwide[17]. The unpredictable and sudden seizures characteristic of epilepsy result in a high disability and mortality rate, and causing a severe mental pressure and disease burden on both patients and society as a whole[18]. Presently, nearly 50% of epilepsy cases have no discernible cause, making it challenging to develop effective targeted treatments[19]. This not only contributes to the development of refractory epilepsy but also leads to a high recurrence rate[20]. Therefore, investigating potential unknown etiologies of epilepsy is crucial for accurate treatment of this disease.

As a nervous system disease with a heavy disease burden, epilepsy is closely associated with several other nervous system diseases[21]. For instance, epilepsy shares several clinical features with migraine, such as episodic attacks, triggering factors, presence of aura, and frequent familiarity[22]. Additionally, they share several mechanisms such as cortical spreading depression[23]. PFO has been found to affect stroke and migraine through mechanisms such as paradoxical embolization, microembolus triggered cortical spreading depression, and low oxygen saturation. It is possible that PFO may also be a risk factor for refractory epilepsy patients by these mechanisms. Based on this, we propose the hypothesis that PFO is an independent risk factor for refractory epilepsy and that PFO closure may helpful to control seizures in these patients.

In our preliminary work, we screened epilepsy patients at the Epilepsy Center of West China Hospital at Sichuan University for patent foramen ovale (PFO) using contrast-enhanced transthoracic echocardiography. We found that the prevalence of PFO was much higher in epilepsy patients than in the general population (PFO prevalence: 38.69%). Additionally, we observed a higher incidence of epilepsy in the PFO cohort than in the normal population (Epilepsy incidence: 2.15%). Furthermore, we conducted surgical treatment on 28 refractory epilepsy patients with PFO, and found that both seizure frequency and severity decreased significantly during the 2-year postoperative follow-up period. Building on these research results, we conducted a clinical randomised trial to provide powerful evidence for the efficacy of PFO closure in refractory epilepsy patients with PFO.

**4. Study purpose and design**

The PFOC-RE trial is a prospective, open-label, randomized, parallel-controlled study designed to investigates the efficacy and safety of PFO closure surgery for the treatment of refractory epilepsy patients, and PFOC-RE followed a 1:1 allocation ratio and was an superiority trail. The primary aim of the trial is to assesses the capacity of PFO closure surgery to alleviate epileptic seizures in patients with epilepsy and PFO.

**5. Methods: Participants, interventions and outcomes**

**5.1** **Study setting and procedure**

This prospective, open-label, randomized, parallel-controlled clinical trial is conducted in the Epilepsy Center at the West China Hospital of Sichuan University. This study aims to evaluate the efficacy and safety of PFO closure for relieving epileptic seizures in patients with refractory epilepsy accompanied by PFO of second-grade or higher levels of RLS (PFOC-RE). The trial was registered on November 11, 2022, and the enrollment of all participants began on December 1, 2022. This trial is registered in the Chinese Clinical Trial Registry (ChiCTR2200065681).

After completing clinical screening and signing an informed consent form, all participants are randomized in a 1:1 ratio into the intervention or control group. Subjects assigned to the intervention group will undergo a PFO closure procedure and receive antiplatelet therapy for 24 weeks, while those in the control group will only receive antiplatelet therapy for 24 weeks, which is consistent with the medication regimen of the intervention group. All participants will be followed-up for 48 weeks. During the follow-up period, seizure characteristics including frequency, duration, severity, quality of life, and adverse safety events will be recorded to evaluate the efficacy and safety of the trial. The overall design flow chart is shown in Figure 3, and the detailed study period is presented in Table 1.

**5.2 Participants Eligibility**

Participants included not only patients but also the staff of the research team. For patients, we set a series of inclusion and exclusion criteria, which could seen in Supplement file 3, and for practitioners, we also set recruitment conditions and training procedures.

Inclusion criteria

1.It conforms to the diagnostic criteria for epilepsy by the International League Against Epilepsy, i.e., ILAE (2014 version).

2.It conforms to the diagnostic criteria for refractory epilepsy by the ILAE (2010 version).

3.It conforms to the diagnostic criteria for PFO by the American Society of Echocardiography (ASE) and Society for Cardiac Angiography and Intervention (SCAI) (2015 version). Participants are required to have a second or higher grade of RLS, detected using transthoracic echocardiography with contrast injection, as shown in Figure 4 [2].

4.Patients aged 18 to 55 years-old, who can complete the epilepsy diary independently or with the help of family members.

5.Participants should have at least one epileptic seizure observed during the 6-week recruitment screening period and confirmed by a 24-hour video electroencephalogram (EEG) immediately after the seizure.

6.Participants are required to maintain a stable antiepileptic medical therapy during the screening period and throughout the trial, and to keep their medication regimen as unchanged as possible without an emergency event.

7.Participants were required to have a valid documented epilepsy diary for at least 4 weeks during the recruitment screening period.

8.Participants should agree to participate in this trial and sign an informed consent.

Exclusion criteria

1.Participants with history of pseudo-seizure.

2.Participants with serious mental illness, such as anxiety or depression.

3.Participants with cognitive dysfunction (Mini-Mental State Examination score ≤ 23).

4.Participants with vascular puncture site infection or difficult puncture.

5.Participants with PFO associated with other cardiac structural abnormalities, such as moderate or higher valvular regurgitation and pulmonary hypertension.

6.Participants who have contraindications for antiplatelet therapy such as open trauma fracture surgery, gastrointestinal ulcers, active bleeding, and visceral bleeding three months before the screening period.

7.Participants with existing severe systemic diseases, such as digestive, circulatory, respiratory, liver, urinary, musculoskeletal, immune, or genetic metabolic diseases, whom researchers judge might be a potential impact on the results of the trial.

8.Participants who received head surgery or neuromodulation.

9.Participants under consideration for seizure-related surgery or any surgery involving general anesthesia, or who were already under general anesthesia four weeks before the screening period.

10. Participants who receive vaccinations during the screening period or four weeks before.

11. Participants preparing for pregnancy or breastfeeding during the trial period or three months after the study.

12. Patients who are participating in other interventional clinical studies during the trial.

13.Participants who are planning to travel or live abroad during the study period and cannot be followed-up.

14.Participants deemed inappropriate by the researchers for other reasons (need for detailed recording).

**Table 1. Schedule of enrolment, intervention and assessment according to the Standard Protocol Items: Recommendations for Interventional Trials (SPIRIT) statement**

|  | **Study Period** | | | | | | | | |
| --- | --- | --- | --- | --- | --- | --- | --- | --- | --- |
|  | **Screening** | **Enrolment** | **Allocation** | **Intra-operation** | **Post-operation** | | | | **Close - out** |
| **Time Point*** | **-7 to -2** | **-1** | **-1** | **0** | **4** | **12** | **24** | **48** |  |
|  | | | | | | | | | |
| **Screening** | | | | | | | | | |
| **General information** | **X** |  |  |  |  |  |  |  |  |
| **Eligibility screening** | **X** |  |  |  |  |  |  |  |  |
| **Epilepsy diary** | **X** |  |  |  |  |  |  |  |  |
| **Enrolment** | | | | | | | | | |
| **Informed consent** |  | **X** |  |  |  |  |  |  |  |
| **Allocation** |  |  | **X** |  |  |  |  |  |  |
| **Interventions** | | | | | | | | | |
| **PFO closure** |  |  |  | **X** |  |  |  |  |  |
| **Clopidogrel 75mg** |  |  |  |  | **X** | **X** |  |  |  |
| **Aspirin 100mg** |  |  |  |  | **X** | **X** | **X** |  |  |
| **Assessment** | | | | | | | | | |
| **Seizure frequency** |  |  |  |  | **X** | **X** | **X** | **X** | **X** |
| **Seizure duration** |  |  |  |  | **X** | **X** | **X** | **X** | **X** |
| **Seizure severity** |  |  |  |  | **X** | **X** | **X** | **X** | **X** |
| **Life quality** |  |  |  |  |  | **X** |  | **X** | **X** |
| **Headache score** |  |  |  |  |  | **X** |  | **X** | **X** |
| **Adverse events** |  |  |  |  | **X** | **X** | **X** | **X** | **X** |

**Note: * Times in weeks; PFO, Patent foramen ovale.**

Recruitment of practitioners

The principal investigator will formulate materials containing the information statement and research project protocol consent form. Informed consent will be handed over to each patient and saved strictly. Patients will be recruited according to the predetermined trial recruitment procedure, and all cardiologists and neurologists involved will receive the protocol and training from field workers or through network conferences. Neurologists will be asked to complete an electronic case report form (eCRF) to assess the epilepsy log and relevant risk factors.

To encourage active participation from both participants and researchers, the survey has been designed to be completed in less than 15 minutes. After providing an explanation of the study protocols and goals, all enrolled patients will be required to sign an informed consent form. Researchers and/or research assistants will collect the necessary information, which will be recorded using electronic case report forms (eCRFs) and an online electronic data capture (EDC) system located in the hospital data center. Contributors to the registry will be responsible for data entry and standardization. Once the research is complete and the results are ready to be published, we will share the identified data with others.

**5.3 Informed consent**

Subjects who conform to the inclusion criteria and voluntarily sign informed consent will be included in the study. Subjects are required to sign after carefully reading the informed consent.

A draft version of the informed consent form is provided in supplement draft.

**6. Interventions**

**6.1 Intervention grouping**

Participants in the PFOC-RE trial will be randomly assigned to either the surgical intervention group or the control group. The surgical intervention group will undergo PFO closure surgery and receive antiplatelet therapy for six months. This therapy will include 75mg of clopidogrel and 100mg of aspirin daily for the first three months. From the fourth to the sixth month, the participants will switch to taking 100mg of aspirin daily. Meanwhile, the control group will not receive PFO closure surgery but will still need to undergo antiplatelet therapy for six months with the same medication regimen as the surgical intervention group.

**6.2 Baseline Evaluation**

Baseline protocol-required testing as part of this study are:

- Medical history and risk factors
- Neurology evaluation
- Electrocardiogram (ECG) or Holter study
- Transesophageal echocardiography (TEE) with bubble study
- Magnetic resonance imaging (MRI) or Cat scan (CT)
- Magnetic resonance angiography (MRA), duplex sonography, CT angiography or contrast angiography.

- MRA uses magnetic radio wave energy to look at blood vessels in the body

- Duplex sonography uses high frequency sound waves (Doppler ultrasound) to

measure the size and blood flow through a blood vessel

- CT angiography or contrast angiography uses X-rays and injection of intravenous contrast medium to see the blood flow in the arterial vessel throughout the body

- Pregnancy test (for women of child-bearing potential)
- Blood tests (approximately 4-5 teaspoons or 20-25 ml)

**6.3 Protocol for transesophageal echocardiography (TTE)**

The following recommended protocol for transesophageal echocardiography (TEE) will be used to assure continuity of assessment across study sites. Pre and post-implant echocardiograms should be obtained using image planes in which the atrial septum is perpendicular to the source of ultrasound.

1. Adjusting the instrument

a. Use the highest frequency transducer for patient size.

b. Adjust the transmission power (overall gain) to minimize or eliminate “blooming” of specular reflectors.

c. Adjust the time gain compensation ramp so the image has a uniform brightness to minimize “false positive” dropout in the atrial septum.

d. Place the transmission focus at the depth of the atrial septum.

e. Adjust the color Doppler gain to the point just below the point where random color noise appears.

f. Set the pulse repetition frequency with Nyquist velocity with an approximate range of 35-45 cm/sec.

g. Use a velocity variance map with a “medium” color filter. Set color tissue priority at a level that avoids overlay of color signals onto tissue structures.

h. Perform TEE at 5-7.5 MHz, with all other settings as mentioned above.

i. Perform both longitudinal plane and transverse plane sweeps across the atrial septum.

2. Record 2D Echo in:

a. The Bi-caval longitudinal imaging plane

1. PFO is judged to be present with the visualization of microbubbles in the left atrium within three cardiac cycles from the right atrial opacification at rest and/or during Valsalva release. Evaluate the shunt size by the amount of contrast material that crossed the atrial septum from right to left.

2. The horizontal plane.

3. The aorta from as distally possible to as proximally as possible in the aortic arch.

b. Obtain multiple views of the aortic arch (Omni 90°)

c. Zoom image of left atrial appendage (at least 3 cardiac cycles)

d. Evaluate entire atrial septum including superior region with color flow Doppler in order to exclude sinus venosus defect.

e. Accomplish contrast echocardiography by rapid injection of 5-10ml of isotonic saline solution containing air microbubbles. Perform at least two injections, (1) resting injection and (2) injection with Valsalva maneuver 10 seconds later.

f. Annotate the “Rest” and “Valsalva” injections.

g. Ensure complete opacification of the right atrium. Multiple injections may be required if complete opacification of the right atrium is not obtained. All injections should be labeled as described in 2g.

h. For all digital images ensure that at least 8 cardiac cycles are acquired. Visualization of the initial injection into the right atrium must be included. Ensure annotation of each injection (i.e., “Rest” and “Valsalva”) as per item 2g above.

Note:

TEE will also be used to visualize the presence of an atrial septal aneurysm, which is defined as movement of septum primum greater than or equal to 10mm relative to the plane of the interatrial septum.

An independent Echo Core Lab has been established to review echo tapes of all 6-month TEE videotapes for subjects implanted with a device to evaluate closure of the PFO.

**6.4 Intervention description**

The PFO occluder is a self-expandable, double disc device made from a wire mesh. The two discs are linked together by a short connecting waist. The discs have fabric sewn into them. The fabric used in the device is the same as that used by surgeons to close other cardiac defects. The PFO occluder will remain implanted in patients heart.

Subjects will have the PFO occluder procedure in the cardiac catheterization laboratory, or “cath lab.” Local or general anesthesia will be used and there should not be significant discomfort. This is a non-surgical procedure done using X-ray guidance in which a catheter is inserted through a blood vessel in your thigh up into subjects heart. A catheter is a sterile, flexible, hollow tube that is inserted into a blood vessel to allow for injection or removal of fluids or to pass devices through. After the procedure, subjects may experience some discomfort in the area where the catheter was inserted.

To help doctor evaluate subjects PFO during the procedure, subjects will have a Transesophageal Echocardiography (TEE), angiography and/or maybe intracardiac echocardiography (ICE) done. TEE is an ultrasound test to see subjects’ heart, where an imaging probe is placed through mouth into esophagus (swallowing tube). Some soreness may persist in esophagus for about one week. Angiography is an X-ray of blood vessels or heart chambers filled with a contrast dye that allows doctor to see moving pictures of heart. During angiography, a catheter is passed through a blood vessel in thigh up into heart. If doctor decides to look at heart using ICE, doctors will pass an ICE imaging probe through a blood vessel in thigh up into heart.

After doctor has measured PFO, an PFO occluder is passed through the catheter and positioned in the middle of left atrium. The left disk is deployed, and then drawn against the atrial septum. The right disc is then deployed. After doctor is satisfied with the position of the device, it is released from the delivery cable using a screw mechanism.

The duration of the procedure will be about 1-2 hours. After recovery from anesthesia and a few hours of bed rest, subjects should be able to sit up and walk. Before subjects are discharged from the hospital, a physical exam and electrocardiogram (ECG) will be done to confirm a stable position of the device in your heart. Subjects will be required to take clopidogrel every day for three month and aspirin every day for six months after the procedure.

Doctor may decide to keep you on clopidogrel and aspirin after the required amount of time. To prevent against certain bacterial infections, subjects may need to take some doses of an antibiotic during the first 6 months following the placement of the device, especially if subjects are planning to undergo certain procedures such as dental cleanings. If PFO is not completely closed after 6 months, subjects may continue to receive antibiotics indefinitely for certain procedures.

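### Section 6.4 lets the doctor continue clopidogrel and aspirin after closure without indication, limit or a counterpart for controls, so antiplatelet exposure could differ by arm within the primary outcome window

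*Protocol*

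**What the plan says.** Section 5.1 gives the closure arm 24 weeks of antiplatelet therapy and says of controls that "those in the control group will only receive antiplatelet therapy for 24 weeks, which is consistent with the medication regimen of the intervention group". Section 6.1 sets out the drugs: clopidogrel plus aspirin for three months, then aspirin alone to month six. It says the control group "will still need to undergo antiplatelet therapy for six months with the same medication regimen as the surgical intervention group". In Table 1 (section 5.2) the "Clopidogrel 75mg" row is marked at weeks 4 and 12 and the aspirin row at weeks 4, 12 and 24. Neither is marked at week 48. The table is a single schedule and is not split by arm.

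Section 6.4 describes the occluder procedure and the care that follows it. It restates the course, "Subjects will be required to take clopidogrel every day for three month and aspirin every day for six months after the procedure", and the next paragraph opens with "Doctor may decide to keep you on clopidogrel and aspirin after the required amount of time". It gives no reason for continuing, no maximum duration and no rule for controls. No other section supplies one or overrides the sentence.

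Section 4 describes a "prospective, open-label, randomized, parallel-controlled study". Section 5.1 states "All participants will be followed-up for 48 weeks", and section 10.1 defines the primary outcome over the first year after surgery.

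**The concern.** Giving controls the same antiplatelet course leaves closure as the only planned difference between the arms. Section 6.4 opens a way for that to change after the required course, and it is written for one arm only. The treating doctor can know the allocation, and any extension before week 48 falls inside the period in which seizures are counted.

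Two features of the protocol make this more than a formality. First, its rationale (sections 1 and 2) is that a PFO acts on the brain partly through micro-embolism and paradoxical embolization. Antiplatelet drugs could plausibly bear on that pathway, although the protocol states no effect of them on seizures. Second, section 6.3 provides a core-laboratory review of six-month echocardiograms for implanted participants only, so a natural decision point exists in one arm at about the time aspirin should stop. The protocol does not tie antiplatelet extension to that review.

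Safety is also involved. Section 9 lists bleeding as an anticipated event and section 10.2 counts adverse-event incidence among the secondary outcomes. Longer antiplatelet use in one arm would mix drug bleeding with procedure bleeding.

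**Working it through.** The plan gives no figure on this point to reproduce, and the sample size (88, raised to about 110) does not depend on it. What can be derived is how long exposure could differ.

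**Inputs**
- Follow-up: 48 weeks (section 5.1).
- Required course: clopidogrel to week 12, aspirin to week 24 (Table 1; three and six months in sections 6.1 and 6.4).
- Share of the closure arm extended, f: not given, so assumed.
- Extension in controls: not provided for and not barred; set to zero to obtain a ceiling.

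**Step 1: when discretion begins.** Section 6.4 refers to one required amount of time after a sentence that names two durations. It can be read in two ways.
- Drug by drug: clopidogrel may run on from week 12 and aspirin from week 24.
- Whole course: both drugs may be given after week 24.

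**Step 2: longest possible difference for one participant**, as follow-up minus the start of discretion.

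| Drug and reading | Weeks | Share of follow-up |
|---|---|---|
| Aspirin, either reading | 48 − 24 = 24 | 24/48 = 50% |
| Clopidogrel, drug by drug | 48 − 12 = 36 | 36/48 = 75% |
| Clopidogrel, whole course | 48 − 24 = 24 | 24/48 = 50% |

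If three and six months are taken as 13 and 26 weeks, the drug-by-drug shares become (48 − 13)/48 = 35/48 = 73% for clopidogrel and (48 − 26)/48 = 22/48 = 46% for aspirin. The whole-course share is 46% for both drugs.

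**Step 3: mean gap between arms**, as f × longest difference, if every extension runs to week 48 and no control is extended.

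| f (assumed) | Aspirin, f × 24 | Clopidogrel drug by drug, f × 36 | Clopidogrel whole course, f × 24 |
|---|---|---|---|
| 10% | 2.4 weeks | 3.6 weeks | 2.4 weeks |
| 25% | 6 weeks | 9 weeks | 6 weeks |
| 50% | 12 weeks | 18 weeks | 12 weeks |

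For each f these are upper limits on exposure. No step leads from weeks of exposure to seizures, because the protocol states no effect of either drug on seizure frequency.

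**The case against.** The best reply is that section 6.4 is leftover patient-information text. It addresses the reader as a patient, and the operative regimen is stated consistently in 5.1, 6.1 and Table 1. The disputed sentence applies only once the required course is over, so the required course itself stays equal. This is right as far as it goes: the fault is unregulated discretion after the course, not a second regimen competing with it. But the sentence stands in the protocol's intervention section, and a site following the protocol may act on it.

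A second reply is that continuing antiplatelets after an implant is ordinary device care. Section 9 lists thrombus on the device among the anticipated events. If extension belongs to the closure strategy, comparing strategies remains legitimate. That supports allowing extension for a stated reason. It does not support leaving the reason open, and 5.1 and 6.1 present the two drug regimens as the same.

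Third, a reader might infer that the arms will differ. The documents do not support that. They write the discretion for one arm and are silent on the other; control physicians are not forbidden to continue.

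Fourth, a reader might contrast this with a strict rule for antiepileptic drugs, since inclusion criterion 6 says "Participants are required to maintain a stable antiepileptic medical therapy during the screening period and throughout the trial". The same criterion goes on to ask only that the regimen change as little as possible outside an emergency. It too leaves room for judgement. The contrast that survives is narrow: that rule is common to all participants, whereas the antiplatelet discretion is written for the closure arm.

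**Conclusion.** The point holds as a permitted imbalance in co-treatment. Followed as written, section 6.4 allows antiplatelet exposure to differ by arm for up to 50% of follow-up for aspirin, and up to 75% or 50% for clopidogrel depending on how the required time is read. The 75% figure should not be quoted without that condition.

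These ceilings assume extension to week 48 and none in controls. A reader might conclude that the result could not be attributed to closure. The documents do not support so strong a statement: they give neither how often extension would occur nor what these drugs do to seizures, so neither the size nor the direction of any bias can be derived. The supportable conclusion is that the closure effect and the bleeding comparison could be confounded. This is a worthwhile and cheap improvement, not a flaw that invalidates the design.

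**What to change.** Delete the discretionary sentence in section 6.4. State in section 6.1 that in both arms clopidogrel stops at week 12 and aspirin at week 24. Allow later use of either drug, in either arm, only for a documented clinical indication, for example device thrombus or a vascular event, and record drug, dates and reason in the eCRF.

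The cost is a short amendment to two sections, slightly less clinician discretion and a small recording burden. No visits, tests or participants are added. For anyone already extended, the dates and reasons should be recorded.
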